### Health economic analysis

Cost-effectiveness will be assessed using both trial-based and model-based health economic analyses. Both will follow international methodological guidelines [67–70] and the ‘reference case’ recommended by the National Institute for Health and Care Excellence (NICE) for use in its technology appraisals [71–74], including the use of an NHS and personal social services perspective for costing and discounting of costs and QALYs at an annual rate of 3.5%.

In the trial-based analysis we will use EQ-5D-5L and health and social care resource use data to estimate the costs and QALYs accrued over the 12-month follow-up period by trial participants. In our main analysis we will include costs for all health and social care recorded in the eCRF and reported by patients in the health economics questionnaire at 3, 6, 9 and 12 months. The unit costs of services will be based on national average estimates from published sources [75–78]. We will also conduct a sensitivity analysis including only costs judged by the research team to be potentially related to AF or to AF treatment. QALYs will be estimated from survival data and quality of life (EQ-5D-5L) scores at 0, 3, 6, 9 and 12 months using an AUC approach. EQ-5D-5L scores will be calculated using the 2016 value set for England [79]. Mean between-group differences in QALYs and costs will be estimated using a bivariate regression approach, taking account of correlations between costs and effects and adjusting for any baseline differences in EQ-5D-5L scores or other key patient characteristics (such as age, CHA_2_DS_2_VASc score [congestive heart failure {or left ventricular systolic dysfunction}, hypertension {blood pressure consistently > 140/90 mmHg or treated hypertension on medication}, age ≥ 75 years, diabetes mellitus, prior stroke or transient ischaemic attack or thromboembolism, vascular disease {e.g., peripheral artery disease, myocardial infarction, aortic plaque}, age 65–74 years, sex category {i.e., female sex}] or HAS-BLED score [hypertension, abnormal renal/liver function, stroke, bleeding history or predisposition, labile international normalised ratio, elderly, drugs/alcohol concomitantly]). Multiple imputations will be used to account for missing data if appropriate [39, 65, 69, 80]. If the results indicate a trade-off between costs and health effects, an incremental cost-effectiveness ratio will be calculated—the ‘cost per QALY’. The extent of uncertainty over the results will be estimated using bootstrap regression and presented in the form of a cost-effectiveness acceptability curve [81].

A model-based economic analysis will also be conducted to estimate long-term benefits, harms and costs of surgical and catheter ablation compared with AAD therapy in patients with LSPAF. This will extrapolate costs and health outcomes observed in the trial, including freedom from arrhythmia, utility (EQ-5D-5L scores) and incidence of major side effects, over a long time horizon (up to lifetime). The model will also allow us to estimate costs and outcomes for the trial participants under medical management, which will provide further information about the comparative cost-effectiveness of treatment options for this patient group for healthcare commissioners and research funders. The model will be based on the MAPGuide AF model [82]. This is a discrete event simulation which estimates lifetime costs and QALYs for a heterogeneous population of individuals with AF treated according to a defined pathway of care, including anti-thrombotic and AAD therapy. The base case version of the model reflects the recommended care pathway in the NICE clinical guideline for AF. This care pathway can be changed to estimate costs and QALYs associated with different treatments (e.g., catheter ablation, thoracoscopic surgical ablation or AAD).

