**Methods/design:**

Catheter Ablation versus Thoracoscopic Surgical Ablation in Long Standing Persistent Atrial Fibrillation (CASA-AF) is a prospective, multi-centre, randomised controlled trial within three NHS tertiary cardiovascular centres specialising in treatment of atrial fibrillation. Eligible adults (*n* = 120) with symptomatic, long-standing, persistent atrial fibrillation will be randomly allocated to either catheter ablation or thoracoscopic ablation in a 1:1 ratio. Pre-determined lesion sets will be delivered in each treatment arm with confirmation of appropriate conduction block. All patients will have an implantable loop recorder (ILR) inserted subcutaneously immediately following ablation to enable continuous heart rhythm monitoring for at least 12 months. The devices will be programmed to detect episodes of atrial fibrillation and atrial tachycardia ≥ 30 s in duration. The patients will be followed for 12 months, completing appropriate clinical assessments and questionnaires every 3 months. The ILR data will be wirelessly transmitted daily and evaluated every month for the duration of the follow-up. The primary endpoint in the study is freedom from atrial fibrillation and atrial tachycardia at the end of the follow-up period.

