##### Post-operative analgesia

Participants in the surgical ablation arm will receive intercostal nerve block at each port site (bupivacaine or similar agents; dosage depending on patient characteristics and tolerance), paracetamol (1 g four times daily intravenously or per rectum and then by mouth) and codeine (30–60 mg up to four times daily). Patients can also be given tramadol (50 mg intramuscularly) if appropriate. In the first 24 h post-procedure the patient will be receiving patient-controlled analgesia with fentanyl or morphine or other opioids, depending on the anaesthetist’s recommendations and current clinical practice. Opiates should be reduced 12 h post-operatively.

One day after surgery, if patients have normal renal function and are able to tolerate oral medication, analgesia could be provided by non-steroidal anti-inflammatory drugs for 1 week with or without opiates. On discharge, the patients will have a supply of analgesics for 28 days to be taken as needed. Participants in the catheter ablation arm will be treated with paracetamol and codeine as required.

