##### Early post-operative discharge period

Following discharge, study participants will be contacted by the research team once per week for the first month to assess their health status. They will be asked about pain management, cough, raised temperature, difficulties swallowing and any other symptoms that may be early indications of possible complications. In addition, patients will be advised to contact the study team if they have any concerns regarding their health for the duration of the study. If deemed appropriate the patients will be brought back to the study centre for full assessment, evaluation and treatment of health issues, even if the likelihood of those issues being related to study procedures is remote.

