### Data from imaging modalities and questionnaires

cMRI will be performed during the baseline visit and again at 6 months after the ablation. It will be used to capture LA area and length [56, 57] and to calculate maximum and minimum LA volumes as well as the cross-sectional diameter of PVs. The images will be acquired using planes in the LV long- and short-axis stacks. A specific protocol of sequences for late gadolinium enhancement (LGE) of the LA will be used to evaluate location and quantification of LA scars [58]. The LV function will also be measured by volume quantification in systole and diastole using endocardial tracing [59–61].

TTEs will be performed at baseline, 3 months after the ablation and at the last study visit (12 months after the ablation). In addition to the standard clinical protocol set out by British Society of Echocardiography, we will acquire images to allow for offline assessment of LA function (measurement of myocardial velocities, LA strain and strain rate) by using tissue Doppler and 2D speckle-tracking methods [62–64].

The EHRA symptoms score and AFEQT and EQ-5D-5L questionnaires will be used at each study visit to assess any changes in patients’ symptoms and quality of life from baseline to the end of the follow-up period [39, 65, 66]. We have also designed a health economics questionnaire to collect patient-reported data on the use of primary, secondary and community health and social care services following ablation to estimate costs.

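### The within-trial QALYs use no EQ-5D-5L score between 0 and 3 months, so early post-procedural utility loss is omitted, which probably but not certainly favours surgery

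*Protocol article*

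**What the plan says.** The Health economic analysis section states the rule: QALYs come from survival and "quality of life (EQ-5D-5L) scores at 0, 3, 6, 9 and 12 months using an AUC approach". The rest of the article agrees with that schedule. The abstract has patients "completing appropriate clinical assessments and questionnaires every 3 months", and the section on imaging and questionnaires says that "AFEQT and EQ-5D-5L questionnaires will be used at each study visit".

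There is contact with patients between 0 and 3 months. Under Early post-operative discharge period, "study participants will be contacted by the research team once per week for the first month to assess their health status". The stated content is clinical: "They will be asked about pain management, cough, raised temperature, difficulties swallowing". No EQ-5D-5L is mentioned there.

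The two arms are described as recovering differently. The surgical procedure uses three ports on each side, and the section on post-operative anticoagulation refers to chest drains. The analgesia section gives surgical patients intercostal blocks and, for the first 24 hours, "patient-controlled analgesia with fentanyl or morphine or other opioids". It continues, in the text on surgical patients: "On discharge, the patients will have a supply of analgesics for 28 days to be taken as needed". Catheter patients receive paracetamol and codeine as required.

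Costs over the same weeks are counted, from the eCRF and from the health economics questionnaire, which is first completed at month 3.

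**The concern.** Taking the score at 0 as the pre-ablation baseline, the AUC joins it to the month-3 score by a straight line. Recovery from the index procedure takes place inside that interval, at the same point for every patient, and nothing is measured there. The costs of recovery enter the numerator of the cost per QALY, while a transient loss of health in the same weeks does not enter the denominator.

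If the loss were equal in the two arms, it would cancel in the comparison. The article's own description suggests that it is not equal. QALYs and cost-effectiveness are named secondary outcomes, and expected QALY differences over 12 months are small, so an omission of one or two hundredths of a QALY could matter.

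The planned methods do not repair this. Adjustment for baseline EQ-5D-5L uses only the score at 0. Multiple imputation needs some patients with observed values in the interval, and the plan provides none.

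**Working it through.** **Figures in the plan.** The article states no utility, decrement or QALY figure, so there is none to reproduce. Its one reproducible design figure is the sample size: 76% versus 44%, 90% power, 5% significance (taken as two-sided), pooled variance, mean proportion 0.60.

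n = [1.960 × √(2 × 0.60 × 0.40) + 1.282 × √(0.76 × 0.24 + 0.44 × 0.56)]² / 0.32² = (1.358 + 0.839)² / 0.1024 = 47.1, so 48 per group, and 96 × 1.25 = 120. This agrees with the article. It does not bear on the point, except that the 32-point difference is used below.

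**AUC weights.** With scores at 0, 3, 6, 9 and 12 months, the trapezoid weights are 0.125, 0.25, 0.25, 0.25 and 0.125 years. No weight falls on any time between 0 and 3 months.

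**What the schedule returns.** Assume an excess surgical loss of 0.20 just after the procedure that recovers linearly over 6 weeks.
- True loss: 0.20 × 6/52 ÷ 2 = 0.0115 QALY.
- Loss on the planned schedule: 0.0000, because the scores at 0 and at month 3 are unaffected.

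**If part of the loss remains at month 3.** Let the 0.20 loss fall linearly to a residual r at month 3 and to zero at month 6. True loss = (0.20 + r)/2 × 0.25 + r/2 × 0.25. Measured loss = 0.25 × r.
- r = 0.02: true 0.030, measured 0.005, missed 0.025.
- r = 0.05: true 0.0375, measured 0.0125, missed 0.025.

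**Range of the omission.** All decrements and durations are assumed. A constant loss d for w weeks omits d × w/52; linear recovery omits half of that.

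| Excess loss | Constant | Linear recovery |
|---|---|---|
| 0.1 for 2 weeks | 0.0038 | 0.0019 |
| 0.2 for 4 weeks | 0.0154 | 0.0077 |
| 0.3 for 6 weeks | 0.0346 | 0.0173 |

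**Opposing effect: early rhythm benefit.** Suppose that 32 percentage points more surgical patients are arrhythmia-free from the start, each with an assumed utility gain g. The straight line credits half of that gain over the first quarter, so surgery is under-credited by 0.32 × g × 0.25/2.
- g = 0.03: 0.0012 QALY.
- g = 0.20: 0.0080 QALY.

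With these two effects alone, the net error favours surgery only if the excess early loss exceeds:
- linear recovery over 6 weeks: 0.0012/0.0577 = 0.02 to 0.0080/0.0577 = 0.14;
- constant over 4 weeks: 0.0012/0.0769 = 0.02 to 0.0080/0.0769 = 0.10.

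**The case against.** The strongest objection is about direction. A reader might infer that the cost-effectiveness result is shown to be biased towards surgery. The article does not support that.
- It has no utility data for either arm. Both procedures are done under general anaesthesia, so the loss after catheter ablation is not shown to be nil.
- An immediate rhythm benefit would be under-credited, as calculated above. That calculation is generous to the objection: the 32-point difference is a 6-month pilot figure, and during the blanking period anti-arrhythmic drugs may continue and symptomatic recurrence is cardioverted.
- Recurrence after the blanking period leads to an offer of catheter ablation, and the design rates imply more of these in the catheter arm. Dips after repeat procedures can also fall between visits. This is a weaker counterweight than it looks: repeat procedures occur at varying times, and a visit that falls inside a dip is over-weighted, whereas the index procedure always falls in the same unmeasured gap.

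The second objection is about size, and it stands. Patient-controlled analgesia covers 24 hours, and a 28-day supply to be used as needed is a dispensing quantity; it does not show four weeks of reduced utility. A reader might want to express the omission as a share of the QALY gain, but no passage gives that gain.

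A reader might also infer that the error carries into the lifetime model. The article says that the model extrapolates freedom from arrhythmia, utility and major side effects. It does not say that first-year QALYs are carried in, and a dip resolved by month 3 would not change later utilities.

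Finally, the omission is not total. Deaths enter through survival data, and losses that persist to month 3 are partly captured. The assessment schedule in Fig. 2 is not visible here, but an earlier EQ-5D-5L listed there would still be left out of the AUC as stated.

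**Conclusion.** The point stands for the within-trial analysis. It is a matter of arithmetic that the stated schedule gives zero weight to a utility loss that resolves before month 3. That the excess loss is larger after surgery is an inference from the article's description of recovery, so bias towards surgery is probable and not established.

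Under the assumed range, the omission is about 0.002 to 0.017 QALY per surgical patient with linear recovery and 0.004 to 0.035 with a constant loss. The opposing rhythm effect is 0.001 to 0.008 QALY under its own assumptions, so it could cancel the lower part of that range but not the upper part. The effect of repeat procedures cannot be sized from the article. The primary endpoint and the safety outcome are not affected.

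**What to change.** **Patients still to be treated.** Add EQ-5D-5L to the existing weekly contacts in month 1, in both arms from the same date, for example at weeks 1 and 4, and include these scores in the AUC. This also picks up any early rhythm benefit, so it addresses errors in both directions.

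Two extra points do not make the AUC exact. For a 0.20 loss recovering linearly over 6 weeks, the week 1 and week 4 losses are 0.167 and 0.067. The AUC then gives (0.167/2 × 1 + (0.167 + 0.067)/2 × 3 + 0.067/2 × 9)/52 = 0.0141, against a true 0.0115 and a planned 0.0000. The error is much smaller, though of opposite sign.

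**Patients already past month 1.** Keep the planned AUC. Pre-specify a sensitivity analysis that applies the arm-specific early decrement observed in later patients or, if too few remain, an assumed range such as the one above.

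**Cost.** A few minutes on calls already made and a small amendment. The downside is that early values are absent for patients already past month 1. Recruitment opened in August 2015 and the article appeared in February 2018, so this may be many of them, and the observed decrement may rest on few patients. The number of patients under each schedule should be reported by arm.

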## Discussion

The use of traditional pharmacological agents to treat LSPAF is not satisfactory, owing to their serious side effects and need for lifelong treatment. Catheter ablation is widely accepted and effective therapy for paroxysmal AF, but its effectiveness in patients with LSPAF is limited, and multiple ablations may be required to relieve patients of symptoms [83–86]. On the basis of the encouraging results of thoracoscopic surgical ablation in several cohort studies of subjects with persistent AF and LSPAF and our pilot study [45, 87, 88], we have designed this trial to compare the two ablative treatments and provide first-class evidence of their efficacy, safety and cost-effectiveness.

## Trial status

The trial was open to recruitment on 1 August 2015 and currently is actively recruiting at two three NHS specialist care centres (Royal Brompton and Harefield NHS Foundation Trust, Brighton and Sussex University Hospitals NHS Trust and Liverpool Heart and Chest NHS Foundation Trust). Ashford and St Peter’s Hospitals NHS Trust is also registered as a patient identification centre.

## Abbreviations

AAD: Anti-arrhythmic drug
ACT: Activated clotting time
AE: Adverse event
AF: Atrial fibrillation
AFEQT: Atrial Fibrillation Effect on QualiTy-of-Life Questionnaire
AT: Atrial tachycardia
CASA-AF: Catheter Ablation versus Thoracoscopic Surgical Ablation in Long Standing Persistent Atrial Fibrillation
cMRI: Cardiac magnetic resonance imaging
DC: Direct current
DMC: Data monitoring committee
ECG: Electrocardiogram
eCRF: Electronic case report form
EHRA: European Heart Rhythm Association
EQ-5D-5L: EuroQol standardised health questionnaire
FUP: Follow-up
HEQ: Health economics questionnaire
ILR: Implantable loop recorder
LA: Left atrial
LAA: Left atrial appendage
LGE: Late gadolinium enhancement
LSPAF: Long-standing persistent atrial fibrillation
LV: Left ventricular
MRC: Medical Research Council
NICE: National Institute for Health and Care Excellence
NIHR: National Institute for Health Research
NOAC: Novel oral anticoagulant
PPM: Permanent pacemaker
PV: Pulmonary vein
PVI: Pulmonary vein isolation
QALY: Quality-adjusted life-year
SAE: Serious adverse event
SPIRIT: Standard Protocol Items: Recommendations for Interventional Trials
SR: Sinus rhythm
TOE: Transoesophageal echocardiography
TSC: Trial steering committee
TTE: Transthoracic echocardiogram
